#### Outcome assessment

Patient reported general health status prior to surgery and at 6-, 12- and 24-weeks post-surgery using the SF-36 form, the EQ-5D-3L Questionnaire, the SARC-F Index and the Elderly Mobility Scale (EMS).Pain level at the perioperative period and at 6, 12 and 24 weeks postoperatively using the visual analogue scale (VAS) Pain Score.Comparison of perioperative and intraoperative surgical data (delay for surgery, age-adjusted Carlson Comorbidity Index, operation time, fluoroscopy time and dosage, blood loss, length of hospital stay, prescription of pain-killers, osteoporosis assessment using postoperative DEXA of the unaffected hip, union time and intraoperative surgeon related complications, including lag screw malposition, propagation of the fracture, non-anatomical reduction, varus/valgus deformity, rotational deformity and tip-apex distance (TAD) using postoperative CT of the pelvis).Patients’ functional status at 24-week follow-up using the patient reported disease-specific scores (Harris Hip score HHS and Oxford hip score-OHS).

#### Follow-up assessments

All the patients should undergo a clinical and radiological follow-up at 6-, 12- and 24 weeks postoperatively. The follow-up will be concluded by antero-posterior radiographs of the pelvis, lateral radiography of the treated hip and questionnaire like HHS, OHS, SF-36, EQ-5D-3L, EMS, Sarc-f, NPRS scale and Vas score.

### Statistical analysis

The primary outcome measure of device radiological failure is considered a binary outcome (device failed/did not fail). A binary logistic regression model will be performed to assess the association between the outcome of device failure and the predictor of device type (Gamma3, Intertan). The complication rate of G3 versus InterTan at 24 weeks post-operatively would be compared using a chi-squared (at the 5% level). The differences between HHS and OHS between groups will be assessed using an independent samples *t* test at 24 weeks postoperatively at the 5% level. Test levels, will be adjusted using the methods of Holm-Bonferroni to allow for the multiple comparisons. A linear regression analysis will also be used to quantify the effects of the treatment groups on each of the primary outcome measures, after adjusting for the effects of a range of other important, potentially confounding, factors (e.g. age, gender) recorded for each patient.

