**Discussion:**

This study will be the first to compare clinical, radiological and biomechanical measurements of the two different cephalomedullary nails. Our main hypothesis is that the IT nail would provide better radiological outcome and probably better clinical results than the Gama3 nail.

*Clinical trial registration* International Standard Randomized Controlled Trial Number (ISRCTN): https://doi.org/10.1186/ISRCTN15588442, registered on 19/4/2022.

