#### Primary objective

The *primary aim* of this study is to investigate if there are any significant differences in the main radiological measurements (cut-out, varus displacement, loss of reduction, malunion, nonunion) between Gamma3 and IT in closed unstable intertrochanteric fractures (31A2_1–3_) in patients aged over 70 years old at the 24-week follow-up evaluation.

The *second primary aim* would be the functional status at the 24-week follow-up using patient reported disease-specific scores (Harris Hip score HHS-and Oxford hip score-OHS).

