#### Sample size

This study will use two primary clinical outcome measures namely the Oxford Hip Score and the Harris Hip Score. The minimum clinically important differences (MCIDs) for the HHS have been estimated between 7 and 10, whereas for the OHS between 5 and 7. The aim will be to recruit 78 patients in each group as this will provide sufficient participants to obtain a power of 90% for both primary clinical outcome measures. With an allowance for 15% drop-out, the total number of patients required will be 194 (97 in each group). If recruitment proves to be problematic during the course of the trial, then the target will be lowered and the more usual 80% power level will be considered sufficient. For this scenario, the total number of patients required will be 140 (including 15% for drop-out).

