## Discussion

Since the 1960s, the DHS has become the standard implant for surgical treatment of stable intertrochanteric fractures as it allows controlled fracture compression but despite additional modifications, such as trochanteric support plates and antirotational screws, unstable trochanteric fractures are less successfully treated by this method [17–20]. Cephalomedullary nails can provide better lateral wall support in more complex fracture patterns but nevertheless, cut-out of the hip screw has been described as the most frequent mechanical failure for all implants [21–23]. Several studies have shown that the incidence of cut-out for different compression hip screws and cephalomedullary nails ranges from 0 to 16.5% [24–26]. In a recent study by Bojan et al. [27] the primary cut-out rate of Gamma-nail in 3066 consecutive patients was 1.85% and was strongly associated either with unstable fractures involving the trochanteric and cervical regions or the combination of both, non-anatomical reduction and non-optimal screw position which are the only two factors that can be controlled by the surgeon. Recent developments including locking plates, antirotational screws and cement-augmented fixation techniques indicate that the problem of fixation failure is still unresolved [28–31].

The Trigen Intertan (IT) nail (Smith and Nephew) is a current generation IM device, featuring a configuration comprised of a larger superior lag screw and a smaller integrated screw that allows for linear compression of the fragments at the fracture site while providing high rotational stability [32, 33]. Clinical studies evaluating the IT nail against other single screw intramedullary or extramedullary devices have shown controversial results, either similar regarding Harris Hip Score, operation time, blood loss, time to union, mean hospital stay, union problems and perioperative complications [43, 44], inferior, comparing surgical time, blood loss, fluoroscopy usage and intraoperative complications [45–47], or superior in terms of implant failure, mal-union, lag screw cut-out, short term reduction of pain, functional outcomes and uncontrolled varus fracture collapse [33, 48–50].

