Nerhera et al. [51] found that InterTan was clinically more effective when compared to a single screw cephalomedullary nail (PFNA) resulting in fewer complications, fewer revisions and fewer patients complaining of pain. No difference has been established regarding non-unions and Harris Hip Score. Intraoperative outcomes favour PFNA with less blood loss and fluoroscopy usage. The authors concluded that further studies are warranted to explore the cost-effectiveness of these and other implants in managing patients with intertrochanteric fractures.

Date et al. [52] showed that PFNA and Gamma3 had better intraoperative outcomes compared with IT; however, IT had superior implant-related outcomes of cut-out and screw migration. No difference was found between IT and PFNA or Gamma3 in Harris Hip Scores, time to union, malunion and nonunion. The authors suggested that further long-term studies are needed to evaluate clinical outcomes and cost–effectiveness of these cephalomedullary devices.

Onggo et al. [53], reported that InterTan was associated with lower complication rates in terms of all-cause revisions, cut-outs, medial or lateral screw as well as persistent hip and thigh pain. In terms of perioperative parameters, InterTan was associated with longer operative and fluoroscopy times. There was no statistically significant difference in terms of clinical Harris Hip Score and radiological outcomes, non-union, haematoma, femoral fractures, varus collapse, length of stay and mean intraoperative blood loss between the 2 groups. The authors concluded that integrated dual lag screw cephalomedullary nails are associated with fewer revisions and complications but there is insufficient data to suggest that either nail construct is associated with better functional outcomes.

Finally, Quartley et al. [54] in their recent metanalysis of 23 studies (17 with unstable fractures) found that IntetTan reduced the risk of revision/reoperation by 64%, implant failures by 62% and hip and thigh pain by 50% in unstable fractures. No differences were noted between IM nail designs for infection rates, healing time, non-union rates, femoral shortening, or Harris Hip Score. The authors concluded that IT nail may reduce incidence of implant-related complications, hip and thigh pain, and the need for revision/reoperation without compromising clinical and functional outcomes.

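### Radiological device failure is the first-named primary outcome, but the sample size and 90% power rest on the Oxford and Harris Hip Scores alone, and the analysis planned for it is fragile if failures are rare

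*Protocol article*

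**What the plan says.** Three places in the Protocol article put the radiological result first. The Primary objective section says that the primary aim "is to investigate if there are any significant differences in the main radiological measurements", listing cut-out, varus displacement, loss of reduction, malunion and nonunion. Functional status by Harris Hip Score (HHS) and Oxford Hip Score (OHS) follows as a second primary aim, and the main Discussion repeats that order. The abstract states: "Our main hypothesis is that the IT nail would provide better radiological outcome and probably better clinical results than the Gama3 nail". The clinical Statistical analysis section opens with "The primary outcome measure of device radiological failure is considered a binary outcome (device failed/did not fail") and assigns it a binary logistic regression on device type. The same section compares the complication rate by chi-squared and HHS and OHS by *t* tests, and applies a Holm-Bonferroni adjustment.

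The Sample size section has a different starting point: "This study will use two primary clinical outcome measures namely the Oxford Hip Score and the Harris Hip Score". It quotes minimum important differences for those scores and claims 90% power for both with 78 per group. Radiological failure does not appear there.

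The Statistical analysis section adds: "A linear regression analysis will also be used to quantify the effects of the treatment groups on each of the primary outcome measures", adjusted for factors such as age and gender.

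**The concern.** The outcome that carries the main hypothesis has no size basis, while the 90% figure stands as the trial's only statement of power. A reader could take it to cover the radiological comparison. If failures are uncommon, a non-significant radiological result would say little, yet it could be reported as showing that the two nails perform alike. An unsettled ranking also leaves room to decide after the results which outcome is presented as primary.

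Two analysis choices add to this. Ordinary logistic regression gives an infinite or undefined odds ratio when an arm has no failures. Linear regression for each primary outcome, read literally, also applies to an outcome just described as failed or not failed.

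**Working it through.** **The plan's own figure.** The 78 per group cannot be recalculated because the article gives no standard deviation. Inverting the two-sample formula at two-sided 5% and 90% power gives (1.960 + 1.282) × √(2/78) = 0.519 SD. With the quoted differences this implies an SD of 9.6 to 13.5 for OHS (5/0.519 to 7/0.519) and 13.5 to 19.3 for HHS (7/0.519 to 10/0.519). The figure is therefore a sizing for mean scores. Nothing in it concerns a proportion.

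**Inputs for radiological failure**
- n = 78 evaluable per arm (Sample size).
- Gamma3 failure rate: not given. The Discussion says that "the primary cut-out rate of Gamma-nail in 3066 consecutive patients was 1.85"%, and cites a cut-out range up to 16.5% across implants. These are cut-out rates only. Rates of 20% to 40% for the five-part outcome are assumptions.
- Effect: a meta-analysis cited in the Discussion found that InterTan "reduced the risk of revision/reoperation by 64%, implant failures by 62"%. The protocol does not adopt this as a design value; it is assumed here. The InterTan rate is then 0.38 × the Gamma3 rate.
- Level: two-sided 5% (sidedness assumed). The first Holm step is 0.05/3 if failure, HHS and OHS form the family (assumed).

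**Method.** Power is the exact sum over two binomial distributions of all outcomes where the uncorrected Pearson chi-squared statistic is significant. This is the score test of a logistic model with device type as the only predictor, so it is a fair stand-in for the planned model. The chance of an empty arm is 1 − [1 − (1 − p₁)⁷⁸][1 − (1 − p₂)⁷⁸]. At 5%, for example, 0.95⁷⁸ = 0.018 and 0.981⁷⁸ = 0.224, so 1 − 0.982 × 0.776 = 0.238. The required n is [1.960√(2p̄(1−p̄)) + 1.282√(p₁(1−p₁) + p₂(1−p₂))]² / (p₁ − p₂)², before dropout.

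| Gamma3 v InterTan | Expected failures | Power, 5% | Power, 0.05/3 | An arm with none | n per arm for 90% |
|---|---|---|---|---|---|
| 1.85% v 0.70% | 1.4 v 0.5 | 3.4% | 0.2% | 68% | 2011 |
| 5% v 1.9% | 3.9 v 1.5 | 16.8% | 6% | 24% | 727 |
| 10% v 3.8% | 7.8 v 3.0 | 34.5% | 20% | 5% | 350 |
| 16.5% v 6.27% | 12.9 v 4.9 | 53.6% | 37% | 0.6% | 201 |
| 20% v 7.6% | 15.6 v 5.9 | 63% | 46% | 0.2% | 161 |
| 30% v 11.4% | 23.4 v 8.9 | 84% | 70% | <0.1% | 98 |
| 40% v 15.2% | 31.2 v 11.9 | 95% | 88% | <0.1% | 67 |

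By the normal approximation, 90% power at the unadjusted level needs a Gamma3 rate of about 35.6%. Under the fallback of 140 patients (70 per arm, about 59 after 15% loss), exact power over the cited cut-out range is 1.6% to 42.5%. If all 97 recruited per arm were evaluable, the normal approximation gives 61% at 16.5%.

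**The case against.** Several points on the other side stand.

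- **The outcome is wider than cut-out.** It covers "main radiological measurements (cut-out, varus displacement, loss of reduction, malunion, nonunion"), and the Radiographic evaluation section counts varus collapse from 3°. Its rate could well exceed 16.5%, and at 40% power would be 95%. A reader might infer that the trial has at most 54% power, or cannot answer its main question. The documents do not support that.
- **The sections can be read together.** The Sample size section speaks of primary *clinical* measures, which is compatible with a radiological and a functional co-primary aim. This is less a flat contradiction than a ranking not stated in one place and a size basis missing for the first-ranked aim.
- **Chi-squared is assigned to the complication rate**, not to device failure, so the sparse-data objection properly concerns the logistic model.
- **The empty-arm problem is confined to low rates.** At 16.5% it is under 1%.
- **The 0.05/3 figures are floors.** The Holm family is not defined, and later steps are less strict.
- **The literature does not split cleanly.** It is tempting to say the trial is sized where its own sources expect nothing. However, the Discussion also cites studies with better function on InterTan, and some of its reviews found no difference in varus collapse, malunion or nonunion.
- **The linear regression sentence follows the HHS and OHS tests** and may have been meant for them only. Its wording still covers every primary outcome.

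None of this supplies a rate, target difference or power for radiological failure.

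**Conclusion.** The point holds in a conditional form. The first-ranked outcome has no sample-size basis, and the 90% claim belongs to HHS and OHS alone. How far power falls short depends on a composite failure rate the article does not give: about 3% to 54% over the cited cut-out rates, 63% to 84% at assumed rates of 20% to 30%, all with an assumed 62% reduction at an unadjusted 5% level. These are scenarios, not the power of the trial. The risk that the logistic model fails is material at about 2% to 5% and negligible at 16.5%. The linear regression wording is wrong for a binary outcome as it stands.

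**What to change.** 1. Make Primary objective, Sample size, clinical Statistical analysis and the main Discussion state one hierarchy. In Sample size, say that the 90% power applies to HHS and OHS only and that the trial is not sized for radiological failure.
2. In Statistical analysis, analyse device failure by Firth (penalised) or exact logistic regression. Report the risk difference with a 95% confidence interval suited to sparse data, and state that a non-significant result is not evidence of equivalence.
3. Limit the adjusted linear regression to HHS and OHS, and use penalised logistic regression for the adjusted analysis of failure.

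The cost is a little more analysis work and a less favourable power statement; neither the number of patients nor the follow-up changes. Moving failure to a secondary outcome, or adding a continuous measure such as change in neck-shaft angle, is open to the sponsor but not required.

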#### Radiographic evaluation

A standard technique will be kept, in order to have the same parameters in all radiographs. For the antero-posterior ones of the pelvis, both legs of the patients will be rotated inwards 15°. The radiographic measurements will be monitored by two distinguished examiners through RadiAnt DICOM Viewer. Intra-class correlation coefficients (ICC) will check the inter- and intra-rater reliability. The parameters that will be radiographically evaluated are the TAD, the position of the chephalomedulary nail in the femur head and the alignment [42]. Moreover, throughout the follow-up the varus malalignment of the implant will be assessed, as well as the cut-out of the nail and the percentage of nonunion or malunion. Varus collapse is a rotation of the proximal part of the femur anteriorly for at least 3°.

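### Device failure, the first primary outcome, is to be analysed by ordinary logistic regression, which gives no finite odds ratio if an arm has no failures and, with the usual Wald test, is conservative when failures are few

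*Protocol article*

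**What the plan says.** The Statistical analysis section of the clinical study defines the outcome: "The primary outcome measure of device radiological failure is considered a binary outcome (device failed/did not fail". It then fixes the method: "A binary logistic regression model will be performed to assess the association between the outcome of device failure and the predictor of device type". It does not say whether the test is Wald, likelihood-ratio or score, and gives no alternative for very few failures. A chi-squared test at the 5% level is planned for the 24-week complication rate.

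The Primary objective section describes the outcome as the "main radiological measurements (cut-out, varus displacement, loss of reduction, malunion, nonunion". No expected rate is stated for this set. The Discussion gives rates for one component only: "the incidence of cut-out for different compression hip screws and cephalomedullary nails ranges from 0 to 16.5" per cent, and "the primary cut-out rate of Gamma-nail in 3066 consecutive patients was 1.85" per cent. It also reports, from a meta-analysis, that InterTan reduced "implant failures by 62" per cent in unstable fractures.

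The Sample size section rests on the Harris and Oxford hip scores: 78 per group before drop-out, with a permitted reduction to 140 patients in total including drop-out.

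**The concern.** With a single two-level predictor, maximum-likelihood logistic regression estimates the log odds ratio directly from the 2×2 table. If one cell is zero, the estimate runs off to infinity and so does its standard error. The Wald p-value then goes to about 1 however clear the difference is. With small but non-zero counts the Wald test stays defined but rejects too seldom.

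The article expects InterTan to give the better radiological outcome. If that is right, the InterTan arm is the one likely to become sparse. The trial could then report an unusable odds ratio, or a non-significant Wald test where the chi-squared test would reject, on a primary outcome. A method chosen after an empty arm has been seen would be open to the charge of selection.

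**Working it through.** **Inputs.** Evaluable patients per arm: 78 (Sample size). Fallback: 140 / 2 = 70 recruited per arm; 70 × 0.85 = 59.5, taken as 59. Level 5% (Statistical analysis), taken as two-sided. Relative risk 1 − 0.62 = 0.38, from the implant-failure figure in the Discussion; applying it to the whole radiological outcome is an assumption. The Gamma3 risks of 5%, 10% and 30% are also assumptions, chosen to show a range; 1.85% and 16.5% are the article's cut-out figures. The plan states no power or event count for device failure, so there is no figure of its own to reproduce.

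**1. An empty arm.** Let a and b be the failures out of n per arm.

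- Odds ratio = a(n − b) / [b(n − a)].
- SE of its log = √[1/a + 1/(n − a) + 1/b + 1/(n − b)].

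At b = 0 neither is finite. Take 6/78 v 0/78:

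- Wald: p ≈ 1; the fit does not converge.
- Pearson chi-squared: pooled risk 6/156 = 0.0385; (6/78)² / (0.0385 × 0.9615 × 2/78) = 6.24, p = 0.012.
- Firth penalised likelihood ratio: p = 0.012.
- Fisher exact: p = 0.028.
- Ordinary likelihood ratio: p = 0.003.

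**2. How often an arm is empty.** P = 1 − [1 − (1 − p₁)ⁿ][1 − (1 − p₂)ⁿ]. At 5% v 1.9%: 0.95⁷⁸ = 0.018 and 0.981⁷⁸ = 0.224, so P = 1 − 0.982 × 0.776 = 0.238.

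**3. Power.** All 2×2 tables were enumerated and weighted by the two binomial probabilities. A table with an empty arm counts as non-significant for Wald. Results for 78 per arm:

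| Gamma3 v InterTan risk | Wald | Likelihood ratio | Chi-squared | Firth | Empty arm |
|---|---|---|---|---|---|
| 1.85% v 0.70% | 0.0% | 10.7% | 3.4% | 0.9% | 67.5% |
| 5% v 1.9% | 1.8% | 25.0% | 16.8% | 11.6% | 23.8% |
| 10% v 3.8% | 21.8% | 36.6% | 34.5% | 30.8% | 4.9% |
| 16.5% v 6.3% | 48.7% | 53.7% | 53.6% | 52.9% | 0.6% |
| 30% v 11.4% | 82.4% | 83.7% | 83.7% | 83.3% | about 0% |

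**4. Type I error at 78 per arm.** With a common risk of 3%: Wald 0.1%, chi-squared 4.4%. With 5%: Wald 1.2%, chi-squared 4.9%. The likelihood-ratio test reaches 8.4% at a common risk of 1.85%, so its higher power at low rates is partly bought with an inflated error rate.

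**5. The permitted smaller trial, 59 per arm.** Wald v chi-squared power is 0.4% v 12.3% at 5% v 1.9%, and 9.9% v 25.6% at 10% v 3.8%. An empty arm has probability 35.5% and about 10%.

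**6. Limit of the remedy.** At 1.85% v 0.70%, about 2,011 patients per arm would be needed for 90% power. There the shortfall comes from sample size, not from the choice of test.

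**The case against.** The tempting stronger reading is that the planned logistic regression loses most of its power at the failure rates the article cites. The documents do not support that, for four reasons.

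- **No Wald test is named.** For one binary predictor, the score test of the same logistic model is the Pearson chi-squared test, and its likelihood-ratio test does not lose power. Only the Wald statistic does. The choice among them is detail that a condensed article may leave to an analysis plan, and none is shown here.
- **The cited rates are for cut-out alone.** The outcome lists five components, and one has a low threshold: "Varus collapse is a rotation of the proximal part of the femur anteriorly for at least 3" degrees. If failure means any of the five, its rate is at least the cut-out rate and may be well above it. The 1.85% comes from consecutive patients, whereas this trial enrols only unstable fractures.
- **The 62% reduction is for implant failures.** The Discussion reports no difference in nonunion from the same meta-analysis, and none in malunion or varus collapse from other reviews. A relative risk of 0.38 for the whole outcome may be too favourable.
- **The loss fades as failures become common**, and at the lowest rates no test has useful power.

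All four stand and limit the size of the point. It could also be said that the chi-squared test for complications already covers failures, since the Limitations section counts cut-out and varus displacement among complications. That is arguable, because Table 1 lists failure rates on a separate line.

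What remains is that the article does fix a model for a primary outcome, and that its maximum-likelihood odds ratio is undefined with an empty arm whichever test accompanies it.

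**Conclusion.** The point holds in a limited form. The undefined odds ratio with an empty arm is certain and needs no assumption. How likely that is, and how much power is lost, depends on three things the article does not state: the failure rate of the radiological outcome, the treatment effect on it, and the use of a Wald test.

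Under the assumptions above, the Wald test gives up about 15 percentage points at a Gamma3 risk of 5% (16.8 − 1.8), 13 at 10% (34.5 − 21.8), 5 at 16.5% (53.6 − 48.7) and 1 at 30% (83.7 − 82.4). The choice thus matters mainly at about 10% or below, and more if the trial falls back to 140 patients. It would be wrong to conclude that a true advantage would be missed only because of the test: at 5% v 1.9% the chi-squared test itself has only 17% power. This is an inexpensive improvement to a primary analysis, not a flaw that invalidates it.

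**What to change.** Change the analysis wording for device failure as follows:

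- Test it with the chi-squared (score) test already planned for complications.
- Report the risk difference with a score-based 95% confidence interval, which stays defined when an arm has no failures.
- Fit any logistic model of device failure, including an adjusted one, by Firth penalised likelihood with profile-likelihood intervals and tests.

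Stating the expected rate of the radiological outcome would also let a reader judge how sparse the data may be.

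The cost is about two sentences and a penalised routine beyond the default menu. If failures prove common, almost nothing is lost: at 30% v 11.4% the chi-squared and Firth tests have 83.7% and 83.3% power against 82.4% for Wald. The change does not make the trial adequately powered for rare failures; that is a matter of sample size.

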#### Randomization

Randomization sequence will be created using Stata 9.0 (StataCorp, College Station, TX) statistical software and will be stratified with a 1:1 allocation ratio using random block sizes of 2, 4, and 6. An investigator not involved in the main study will perform the randomization process. These data will be stored on computer and will be available at the day of the intervention.

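### Allocation is stated to be stratified, but the t tests fixed for HHS and OHS carry no stratum term, so they are conservative if the strata predict outcome

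*Protocol article*

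**What the plan says.** All references are to the clinical part of the protocol article.

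- **Randomization:** the sequence "will be stratified with a 1:1 allocation ratio using random block sizes of 2, 4, and 6". The article does not say by what it is stratified, here or elsewhere.
- **Primary objective and Sample size:** HHS and OHS at 24 weeks form the second primary aim, and the sample size rests on them.
- **Statistical analysis, HHS and OHS:** "The differences between HHS and OHS between groups will be assessed using an independent samples *t* test at 24 weeks postoperatively at the 5% level".
- **Statistical analysis, device failure:** "A binary logistic regression model will be performed to assess the association between the outcome of device failure and the predictor of device type". Device type is the only predictor named. The complication rate gets a chi-squared test.
- **Statistical analysis, multiplicity:** "Test levels, will be adjusted using the methods of Holm-Bonferroni to allow for the multiple comparisons".
- **Statistical analysis, adjusted model:** a linear regression is planned in addition, "after adjusting for the effects of a range of other important, potentially confounding, factors (e.g. age, gender) recorded for each patient". The strata are not among the examples, and the model is not said to decide the result.

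**The concern.** Permuted blocks within strata force the arms to be nearly balanced in every stratum. Differences between strata then contribute almost nothing to the true sampling error of the treatment difference. An independent-samples t test does not know this: its pooled variance still includes the between-stratum part. When the strata are related to HHS or OHS, the reported standard error is therefore larger than the true one, the confidence interval is wider than its nominal level requires, and the p value is too large on average.

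The error is on the conservative side, so no extra false positives arise. What is at stake is the precision that stratified allocation makes available and that this analysis leaves unused. That matters most under the reduced recruitment target, where there is less power in reserve.

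**Working it through.** **Inputs from the article.** 78 per arm for 90% power; a fallback total of 140, including 15% drop-out, for 80% power; 5% level.

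**Assumptions.** Two-sided testing (sidedness is not stated). R² is the share of outcome variance explained by the strata, varied because no factor is named.

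**The plan's own figures.** The 78 cannot be derived, because neither an SD nor the chosen difference is given. It can be inverted:

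- d = (1.960 + 1.282) × √(2/78) = 0.519.
- With the quoted MCID ranges this implies an SD of 13.5 to 19.3 for HHS (7/0.519 to 10/0.519) and 9.6 to 13.5 for OHS (5/0.519 to 7/0.519).
- The fallback follows from the same d: n = 2 × ((1.960 + 0.842)/0.519)² = 58.3, so 59 per arm; 59/0.85 = 69.4, so 70 per arm and 140 in total.

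**Formulas.** Let ncp = d√(n/2) and s = √(1 − R²). After stratified allocation:

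- t-test SE is too large by the factor 1/s
- true type I error of the t test = 2 × (1 − Φ(1.960/s))
- power of the t test = Φ((ncp − 1.960)/s)
- power of the strata-adjusted test = Φ(ncp/s − 1.960)

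The ncp is 3.24 at 78 per arm and 2.82 at 59 per arm.

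**Worked case, R² = 0.10, 78 per arm.** s = 0.949. The SE is 5.4% too large. Type I error = 2 × (1 − Φ(2.066)) = 3.9%. Power: Φ(1.351) = 91.2% for the t test, Φ(1.457) = 92.7% adjusted.

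| R² | SE too large by | t-test type I error | Power at 78 per arm, t test / adjusted | Power at 59 per arm, t test / adjusted |
|---|---|---|---|---|
| 0 | 0% | 5.0% | 90.0% / 90.0% | 80.5% / 80.5% |
| 0.10 | 5.4% | 3.9% | 91.2% / 92.7% | 81.7% / 84.4% |
| 0.25 | 15.5% | 2.4% | 93.1% / 96.3% | 83.9% / 90.2% |

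**Simulation check (blocks of 2, 4 and 6).**

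- R² = 0.10, 156 patients, four strata, 3,000 runs: type I error 3.4% unadjusted and 4.8% adjusted; power 91.5% and 93.6%.
- R² = 0.25, two strata, 5,000 runs: with 156 patients, type I error 2.4% and 4.9%, power 92.7% and 96.2%; with 119 patients, 2.4% and 4.7%, and 84.2% and 90.7%.

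These agree with the formulas to within about a percentage point.

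**Device failure.** A simulation with 156 patients in two strata took 16.5% failure in one arm (the top of the cut-out range in the Discussion, used only as an illustration) and an assumed 6% in the other. Power was 51 to 53% without strata and 53 to 55% with them. The standard error of the log odds ratio did not shrink: 0.582 without strata, 0.585 to 0.601 with them.

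**The case against.** **The premise may be loose wording.** The Randomization section never says what the sequence is stratified by, and the trial has one hospital, one fracture class and one age group. If the word only means blocked, the t test is not at fault. This stands, and it is why the conclusion is conditional. The sentence would then need correcting.

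**The planned power is kept.** A reader might infer that the trial is underpowered because the strata are ignored. The documents do not support that. If the strata are prognostic, the single-test power of the t test is at or above the stated figure (91.2% to 93.1% at 78 per arm, 81.7% to 83.9% at 59). Holm-Bonferroni can take the first step below 90%: assuming three tests, 78 per arm gives about 80% at the 1.67% level even with R² = 0. That drop comes from the multiplicity adjustment, not from omitting strata. Adjustment would recover part of it (81.4% to 84.7% at R² = 0.10).

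**The point does not carry over to every test.** A reader might extend the too-wide intervals to the logistic model and the chi-squared test. For the logistic model the simulation shows the opposite for the log-odds-ratio standard error, and only about 2 points of power. The chi-squared test is tied to the complication rate, not clearly to a primary outcome.

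**The adjusted regression could include the strata.** It could, since its covariate list is open, and the detail might sit in a fuller document. But the article itself names the t test, its level and the multiplicity method, and presents the regression as additional. The deciding test is therefore fixed without strata.

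**Conclusion.** The mismatch holds for HHS and OHS: stratified allocation is stated, and the test fixed for these outcomes ignores it. If the strata predict outcome, the standard errors are too large and the tests conservative. With d = 0.519 and two-sided 5%, strata explaining 10% of variance give a type I error of about 3.9% and forgo about 1.5 points of power at 78 per arm, or about 2.7 at 59. At 25% the figures are 2.4%, about 3 points and about 6 points. With strata unrelated to outcome there is no loss.

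No stratification factor is named, so nothing in the document says where in this range the trial lies. What is forgone is extra power and correctly sized intervals; validity and the stated power are not at risk. The improvement is modest but nearly free.

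**What to change.** In the clinical Statistical analysis section, replace the t test as the deciding analysis of 24-week HHS and OHS with a linear model that has treatment and the stratification factor(s) as fixed terms. Enter that model's treatment test into Holm-Bonferroni and keep the t test as supportive. Name the factor(s) in the Randomization section. If the sequence is blocked but not stratified, correct that sentence instead and leave the t test as it is on this account.

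For device failure and complications, a Mantel-Haenszel analysis or a logistic model with the strata would match the design. It should be adopted for consistency, with only a small power gain expected and no narrower log-odds-ratio interval.

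The cost is a change of wording: stratum membership is fixed at randomisation, so no patients or data are added. The model spends a few degrees of freedom, depending on the number of strata. With few failures, strata may be sparse for the binary outcomes, which favours Mantel-Haenszel pooling there. The change should be made before outcome data by arm are seen.
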